# Neoadjuvant stereotactic radiosurgery for intracerebral metastases of solid tumors (NepoMUC): a phase I dose escalation trial

**DOI:** 10.1186/s40880-019-0416-2

**Published:** 2019-11-09

**Keywords:** Cancer, Intracerebral metastasis, Stereotactic radiosurgery, Fractionated stereotactic radiation therapy, Microsurgical resection, Neoadjuvant radiation therapy, Maximum tolerated dose, Protocol

## Abstract

**Background:**

More than 25% of patients with solid cancers develop intracerebral metastases. Aside of surgery, radiation therapy (RT) is a mainstay in the treatment of intracerebral metastases. Postoperative fractionated stereotactic RT (FSRT) to the resection cavity of intracerebral metastases is a treatment of choice to reduce the risk of local recurrence. However, FSRT has to be delayed until a sufficient wound healing is attained; hence systemic therapy might be postponed. Neoadjuvant stereotactic radiosurgery (SRS) might offer advantages over adjuvant FSRT in terms of better target delineation and an earlier start of systemic chemotherapy. Here, we conducted a study to find the maximum tolerated dose (MTD) of neoadjuvant SRS for intracerebral metastases.

**Methods:**

This is a single-center, phase I dose escalation study on neoadjuvant SRS for intracerebral metastases that will be conducted at the Klinikum rechts der Isar Hospital, Technical University of Munich. The rule-based traditional 3 + 3 design for this trial with 3 dose levels and 4 different cohorts depending on lesion size will be applied. The primary endpoint is the MTD for which no dose-limiting toxicities (DLT) occur. The adverse events of each participant will be evaluated according to the Common Terminology Criteria for Adverse Events (CTCAE) version 5.0 continuously during the study until the first follow-up visit (4–6 weeks after surgery). Secondary endpoints include local control rate, survival, immunological tumor characteristics, quality of life (QoL), CTCAE grade of late clinical, neurological, and neurocognitive toxicities. In addition to the intracerebral metastasis which is treated with neoadjuvant SRS and resection up to four additional intracerebral metastases can be treated with definitive SRS. Depending on the occurrence of DLT up to 72 patients will be enrolled. The recruitment phase will last for 24 months.

**Discussion:**

Neoadjuvant SRS for intracerebral metastases offers potential advantages over postoperative SRS to the resection cavity, such as better target volume definition with subsequent higher efficiency of eliminating tumor cells, and lower damage to surrounding healthy tissue, and much-needed systemic chemotherapy could be initiated more rapidly.

*Trial registration* The local ethical review committee of Technical University of Munich (199/18S) approved this study on September 05, 2018. This trial was registered on German Clinical Trials Register (DRKS00016613; https://www.drks.de/drks_web/navigate.do?navigationId=trial.HTML&TRIAL_ID=DRKS00016613) on January 29, 2019.

## Background

Intracerebral metastases are a frequent cause of oncological morbidity and mortality that affect up to 25% of cancer patients; in two thirds of these patients, intracerebral metastasis originates from lung cancer, breast cancer, and malignant melanoma [1–4]. With the introduction of new systemic therapies, a better extracranial tumor control and hence longer survival have been achieved. However, since those new agents barely cross the brain–blood barrier, the incidence of intracerebral metastasis has not been favorably affected [5, 6]. With novel treatment strategies and hence prolonged survival, there is a high demand on safe local strategies with minimal interruption time or delay of systemic treatments. Therefore, efficient management of intracerebral metastasis is a challenge.

Up to date, neurosurgical resection, stereotactic radiosurgery (SRS), fractionated stereotactic radiation therapy (FSRT), and whole-brain radiation therapy (WBRT) are the main treatment modalities for intracerebral metastases [7]. Surgical resection is an effective treatment aiming to relieve symptoms associated with mass pressure by the tumor or surrounding edema. In case of unknown primary resection is mandatory to gain tissue for pathologic analysis. Overall, a patient’s sufficient physical condition is mandatory to undergo such an invasive treatment [8]. First data of the pre-magnetic resonance imaging (MRI) era even suggested an increased overall survival (OS) for patients who underwent the resection of solitary intracerebral metastases [9]. Adversely, about 46%–59% of patients will have a local recurrence due to remnant tumor cells after resection of intracerebral metastases [10, 11]. Over the last decades, several studies have shown that the combination of microsurgical resection followed by WBRT led to lower local and distant recurrence rates compared to surgical resection alone [11, 12]. However, WBRT is also strongly associated with neurocognitive function decline and impaired quality of life (QoL) [13, 14]. Therefore, postoperative radiotherapy (RT) to the resection cavity is now considered to be a treatment of choice, and this technique has shown a superior local control as compared with a surveillance strategy as well as an improved neurocognitive safety profile when compared with WBRT [15, 16]. Despite a lack of comparative evidence, fractionated RT has been shown to be equally efficient, with a convincing safety profile [17, 18]. In case of local or distant recurrence, salvage therapies such as WBRT, SRS, FSRT, and microsurgical resection can be performed [19]. Postoperative FSRT can be initiated after adequate wound healing and is applied to the tumor bed including potential tumor remnants with an extra margin of 1–5 mm to cover microscopic spread and to compensate setup inaccuracies. It has to be taken in account that the resection cavities tend to shrink within a few days after surgery. Therefore, a timely MRI is obligatory for treatment planning [20]. Lately, several studies have focused on neoadjuvant SRS before resection of intracerebral metastases for better target delineation and hence better sparing of surrounding tissue [21–23]. Notably, the inclusion of the surgical tract into the clinical target volume (CTV) is currently recommended by the American Society of Radiation Oncology (ASTRO) guidelines, and neoadjuvant SRS consequently reduces CTV [24].

This trial aims to escalate the dose for neoadjuvant SRS up to the dose thresholds depending on tumor size recommended by the German expert group on stereotactic radiation oncology [25]. Given the improved efficacy of systemic cancer therapies, long-lasting local control becomes of growing importance. Since local FSRT aims to prolong the time interval until the application of WBRT, locally efficient doses have to be applied.

## Methods

### Ethical approval, information, and safety

The experimental setup was approved by the local ethics committee of Technical University of Munich (Registration Number: 199/18S; München, Germany) and conducted in accordance with the Declaration of Helsinki and the Principles of the Good Clinical Practice Guidelines. The regulations regarding medical confidentiality and data protection are fulfilled. A submission to the Bundesamt für Strahlenschutz is not required this was confirmed by the expert commission of the German Society of Radiation Oncology (DEGRO, No. 141) (Additional file 1). The latest version of the protocol is NepoMUC Clinical Trial Protocol Version 1.1, Date August 08, 2018. The SPIRIT© (http://www.spirit-statement.org) checklist was applied for this study protocol.

Informed consent will be obtained from all participants. The participants will be informed about the General Data Protection Regulation (EU) 2016/679 in the informed consent form.

### Data collection, management, and analysis

As used in this study, the term Case Report Form (CRF) should be understood to refer to a paper form or an electronic data record or both, depending on the data collection method used in this trial. For this trial, relevant data will be documented in paper-printed CRFs. All findings including clinical and laboratory data will be documented in the subject’s medical record and in the CRF by the investigator or an authorized member of the study team. The investigator is responsible for ensuring that all sections of the CRF are completed correctly and that entries can be verified against source data. In some cases, the CRF, or part of the CRF, may also serve as source documents: Karnofsky Performance Status, Documentation of Clinical-Neurological Examination. In these cases, a document should be available at the investigator’s site and clearly identify those data that will be recorded in the CRF, and for which the CRF will stand as the source document. There is no financial compensation for the participant. In case that the participant discontinues the study, documented medical parameters will not be collected and used for statistical analysis. In case of deviation from intervention protocol, e.g., no SRS prior to resection, the participant is excluded from the study.

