### Endpoints

The primary endpoint is the MTD for which no dose-limiting toxicities (DLTs) occur. DLTs will be evaluated according to the Common Terminology Criteria for Adverse Events (CTCAE) version 5.0 (2017) continuously during the study until the first follow-up visit (4–6 weeks after surgery) for each patient and each dose level. Central nerve system necrosis (≥ grade 3), cerebrospinal fluid leakage (≥ grade 4), wound infection ((≥ grade 4), wound dehiscence (≥ grade 4), postoperative hemorrhage (≥ grade 4), cognitive disturbance (≥ grade 4), cerebral edema (≥ grade 4), headache (≥ grade 4), and seizure (≥ grade 4) are defined as DLTs.

Secondary endpoints are as follows:Central nerve system necrosis of CTCAE grade 1–3.Cerebrospinal fluid leakage of CTCAE grade 1–3.Wound infection of CTCAE grade 1–3.Wound dehiscence of CTCAE grade 1–3.Cerebral edema of CTCAE grade 1–3.Local control rates.OS and progression-free survival (PFS) at 12-month follow-up.Time interval between treatment initiation of neoadjuvant SRS and start of systemic chemotherapy.Health-related QoL evaluated using the EuroQoL questionnaire.Neurocognitive function assessed using the Minimal Mental State Examination (MMSE) test.Late toxicity of CTCAE grade 1–5.Immunological and molecular parameters [such as programmed death-ligand 1 (PD-L1) expression, Rapidly Accelerated Fibrosarcoma type B (BRAF) gene mutation, epidermal growth factor receptor (EGRF) mutation, and anaplastic lymphoma kinase [ALK] translocation on the resected specimen].

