The primary endpoint of this study is safety assessed from the start of radiotherapy until the first follow up after surgery (4–6 weeks after surgery). Based on experience from clinical practice, the number of patients lost to follow-up is expected to be very small. Patients who dropped out of the study between radiation treatment and first follow-up visit will be replaced by a new patient. For patients without a final examination after 1 year, the last valid examination will be used for the assessment of secondary endpoints. All secondary endpoints will be analyzed in an explorative manner using appropriate statistical methods: Mann–Whitney *U* Test (acute toxicity of CTCAE grade 1–3; late toxicity of CTCAE grade 1–5, immunological parameters, time interval between treatment initiation and start of systemic chemotherapy), Fisher’s exact test or Chi-square test (local control rates), log-rank test and Kaplan–Meier curves (OS and PFS at 12-month follow-up), Student *t* test (neurocognitive function), and scaled *t* test (health-related QoL) for independent patients.

The following parameters will be collected and taken into account in analyses applying regression models: age, Karnofsky performance score, extent of neurosurgical resection, recursive partitioning analysis (RPA)-classification.

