### Assessment of endpoints

The primary endpoint, MTD, will be assessed through extensive anamnesis and clinical neurological examination on the first postoperative day, the day of discharge from hospital, and the first follow-up visit at 4–6 weeks after surgery, with wound healing evaluated by an experienced neurosurgeon. This study will use the CTCAE version 5.0 for toxicity and adverse event reporting. Postoperative MRI (1–2 days after surgery) and the first follow-up MRI (4–6 weeks after surgery) will be evaluated by an experienced neuroradiologist, and the efficacy will be assessed according to the RECIST criteria [34].

For secondary endpoints, anamnesis and clinical neurological examination will be conducted as mentioned above. Disease progression is defined as radiological or neurological/clinical progression (whichever occurs first); PFS is considered the time interval between the date of treatment initiation and the date of disease progression or death, whichever occurs first. If neither event is observed, the patient will be censored at the date of the last follow-up examination. Neurocognitive function, QoL, and late toxicities will be evaluated at each follow-up visit every 3 months or at neurological deterioration (Table 2). Neuropathological work-up on the resected specimen will follow standard operating procedures at the Department of Pathology and will include immunologic as well as molecular parameters, such as PD-L1 expression, BRAF-gene mutation, EGFR mutation, and ALK translocation, where appropriate. Follow-up assessments (including MRI or CT) will be performed as described until disease progression (even after the termination of the study) in accordance with GCP and the treatment guidelines for patients with intracerebral metastases.

**Table 2 Tab2:** Time schedule of this study

Timepoint	Enrollment	Treatment				Follow-up (months)				Close-out (months)
	Day 0	Preoperative RT Day 1	Resection Days 2–7	Postoperative Days 1–2	Postoperative Days 3–5	1,5	3	6	9	12
Enrollment										
Eligibility screening	X									
Informed consent	X									
Study visit	X	X			X	X	X	X	X	X
Planning CT	Within 1–7 days after enrollment									
Planning MRI	Within 1–7 days after enrollment									
Interventions										
Neoadjuvant SRS		X								
Resection			X							
Assessments										
MRI	X			X		X	X	X	X	X
Clinical-neurological examination	X	X	X	X	X	X	X	X	X	X
Minimental state examination	X					X	X	X	X	X
Health-related QoL	X				X	X	X	X	X	X

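### The discontinuation rule excludes data that the secondary-endpoint rules keep for a participant who leaves between the first follow-up visit and month 12

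*Protocol article*

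**What the plan says.** Three places in the protocol article bear on a participant who leaves after the first follow-up visit (4–6 weeks after surgery) and before month 12.

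- **Data collection, management, and analysis:** "In case that the participant discontinues the study, documented medical parameters will not be collected and used for statistical analysis". The sentence has no limit of time or endpoint and no condition about consent.
- **Statistical analyses:** "For patients without a final examination after 1 year, the last valid examination will be used for the assessment of secondary endpoints".
- **Assessment of endpoints**, directly after the PFS definition: "If neither event is observed, the patient will be censored at the date of the last follow-up examination".

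Statistical analyses also has a replacement rule: "Patients who dropped out of the study between radiation treatment and first follow-up visit will be replaced by a new patient". It ends at the first follow-up visit, so it does not cover later departures. The same section says that few patients are expected to be lost to follow-up, without giving a figure.

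The secondary endpoints include "OS and progression-free survival (PFS) at 12-month follow-up", local control and late toxicity of CTCAE grade 1–5. OS and PFS are to be analysed by Kaplan–Meier curves and the log-rank test, and all secondary endpoints are exploratory.

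**The concern.** A participant who leaves at month 6, event-free, is outside the analysis under the discontinuation sentence and inside it under the other two rules. Nothing says which one the analyst should follow.

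The choice matters because deletion conditions the survival sample on something that happens after entry. A patient can discontinue only while still in follow-up, so deleting discontinuers at random removes event-free follow-up and leaves events over-represented. If patients leave because they are doing badly, deletion can instead remove the poorer outcomes.

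Deletion also takes out late toxicity that has already been recorded. In a dose-escalation trial with 3–6 patients per dose level, one deleted patient is between 1/6 = 17% and 1/3 = 33% of that level's late-toxicity data.

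**Working it through.** **The rules side by side, for a participant who leaves at month 6**

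| Endpoint | Discontinuation sentence | Statistical analyses | Assessment of endpoints |
|---|---|---|---|
| PFS, event-free | not used | last valid examination used | censored at last follow-up examination |
| OS | not used | last valid examination used | no rule stated |
| Late toxicity, local control | not used | last valid examination used | no rule stated |

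For PFS the second and third rules are compatible, since both use the patient's information up to the last examination. The conflict is therefore the discontinuation sentence against the other two. For OS it is the discontinuation sentence against Statistical analyses alone.

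**Stated figures.** The article gives no figure for OS, PFS or dropout. Its sample sizes reproduce: 4 × [(3 × 3) + 3] = 48 minimum and 4 × 6 × 3 = 72 maximum.

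**Bias from deletion under random discontinuation.** Assumptions: exponential event times with true 12-month PFS S; independent exponential discontinuation at rate r per 12 months; r and S are not from the article.

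- a = −ln(S) and b = −ln(1 − r)
- Event-free and still in the study at month 12: S(1 − r)
- Discontinued before an event and before month 12: P = [b/(a + b)] × [1 − S(1 − r)]
- Estimate after deletion: S(1 − r)/(1 − P)
- Estimate after censoring at discontinuation: S, unbiased in this model

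Example, S = 0.50 and r = 0.20: a = 0.6931, b = 0.2231, S(1 − r) = 0.40, P = 0.2435 × 0.60 = 0.146. Deletion gives 0.40/0.854 = 0.468, a loss of 3.2 points.

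| True S | r = 2% | r = 5% | r = 10% | r = 20% |
|---|---|---|---|---|
| 0.40 | 0.397 | 0.393 | 0.385 | 0.369 |
| 0.50 | 0.497 | 0.493 | 0.485 | 0.468 |
| 0.60 | 0.597 | 0.593 | 0.586 | 0.570 |

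The loss is 0.3–0.7 points at 2–5% and 1.4–3.2 points at 10–20%.

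**Sensitivity to the definition of the rate.** Above, r is the rate that would apply without events, so r = 20% means that 13–16% actually leave before an event. If instead the share actually leaving between months 1.5 and 12 is fixed at 5%, 10% or 20%, a true 0.50 becomes 0.488, 0.475 or 0.446. The direction is the same and the loss somewhat larger.

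**Sensitivity to the reason for leaving.** Take a baseline 12-month PFS of 0.50, with 20% actually leaving in that window.

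- Hazard doubles after leaving: the truth is 0.463 and deletion gives 0.447 (too low).
- Hazard rises fourfold: the truth is 0.420 and deletion gives 0.446 (too high).

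Censoring gives 0.50 in both cases, so it is not unbiased either when leaving is related to prognosis.

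**The case against.** **A milder reading of the discontinuation sentence.** Data already documented cannot go uncollected, so the sentence may mean only that collection stops at discontinuation. That would agree with the other two rules. The reading is possible, and the full protocol may be clearer. But the sentence speaks of documented parameters and also bars their use in the analysis, which fits deletion better. If the milder meaning is intended, the sentence still needs rewording.

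**Size.** The article expects very small loss to follow-up, and at 2–5% random discontinuation the bias is under 1 point. Even 3.2 points is less than half a standard error at n = 48, where √(0.5 × 0.5/48) = 7.2 points. The endpoints are exploratory. This stands and limits the weight of the point.

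**Stronger readings that the article does not support.**

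- *Three mutually incompatible rules.* The last-examination rule and the censoring rule agree for PFS.
- *A large inflation of OS because patients leave at progression.* If 20–40% of progressing patients left, with 60% progressing by month 12, then 12–24% of all patients would be deleted. The article does not treat progression as discontinuation, and it plans follow-up assessments until progression.
- *A bias that cannot be bounded.* The number of discontinuers will be known, so best-case and worst-case limits can be calculated.
- *A threat to the MTD.* The departures at issue come after the DLT window. The sentence does not expressly protect a completed DLT assessment, but nothing in the article says that one would be withdrawn.

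**Conclusion.** The contradiction stands. For a participant who discontinues between the first follow-up visit and month 12, the discontinuation sentence as written excludes data that the secondary-endpoint rules use, and no precedence is given.

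Following that sentence biases 12-month PFS downward when discontinuation is random, by the amounts calculated above. Those amounts rest on assumed discontinuation rates, exponential times and a true PFS of 40–60%. When leaving is related to prognosis the sign can reverse. The loss of recorded late toxicity does not depend on these assumptions: any deleted patient is a sixth to a third of a dose level.

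This should be corrected, but the effect is confined to exploratory secondary endpoints and is likely to be small if dropout is as low as expected.

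**What to change.** 1. Reword the sentence in Data collection, management, and analysis. Collection stops at discontinuation; data recorded up to that date are kept and analysed; toxicities and recurrences recorded up to then are counted.
2. Remove data only where the patient withdraws consent to the use of data already collected, and report the number removed by dose level.
3. Keep PFS censoring at the last follow-up examination, as Assessment of endpoints has it.
4. Add a separate OS rule that censors at the date last known alive.

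The cost is protocol wording and a check that the consent form matches. No patients or visits are added.

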### Patient selection

Patients with the diagnosis of intracerebral metastasis on contrast-enhanced MRI will be evaluated and screened for the protocol. All patients fulfilling the inclusion and exclusion criteria will be informed about the study. Registration for the study must be performed prior to the initiation of RT. The study treatment (neoadjuvant SRS and/or neurosurgical intervention) should be initiated no later than 3 weeks after diagnosis of intracerebral metastases.

Patients meeting all of the following inclusion criteria will be considered for admission to the trial:Patients with 1–4 intracerebral metastases observed on contrast-enhanced MRI from histologically confirmed solid tumors.One intracerebral metastasis is ≥ 3 cm in diameter orPersisting neurologic symptoms or symptomatic epilepsy from intracerebral metastases despite treatment with steroids.Tumor location close to eloquent brain areas therefore neurological symptoms can be expected without long-term steroidal medication.Patient decides to undergo surgical intervention, if resection and radiotherapy are equal treatment options or if the patient declines radiotherapy.
Age ≥ 18 years of age.Karnofsky performance score ≥ 70, Eastern Cooperative Oncology Group (ECOG) performance score ≤ 1.Women with childbearing potential should have adequate contraception.Ability of subject to understand character and individual consequences of the clinical trial.Written informed consent (must be available before enrolment in the trial).

Patients presenting with any of the following exclusion criteria will not be included in the trial:Patients with unknown primary tumor.The diameter of any single lesion exceeding 4 cm.Tumors causing severe neurological deficits or with mass effect requiring immediate surgical intervention.Previous radiotherapy to the brain.Known histological type of small cell cancer, germ cell cancer, or lymphoma.Patient refuses to take part in the study.Patients who have not yet recovered from acute toxicities of prior therapies.Clinically active renal, liver, or cardiac disease.Known carcinoma within 5 years (excluding carcinoma in situ of the cervix, basal cell carcinoma, squamous cell carcinoma of the skin) requiring immediate treatment that interferes with the study therapy.

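### Exclusion and replacement rules, with no exception for toxicity, can remove an irradiated patient who misses resection from the DLT count, and the DLT window has no defined end without surgery

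*Protocol article*

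**What the plan says.** All references are to the protocol article.

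- **Intervention.** Study design lists SRS, resection and neuropathological evaluation as the treatment. Table 2 puts SRS on day 1 and resection on days 2–7.
- **Exclusion.** Data collection, management, and analysis: "In case of deviation from intervention protocol, e.g., no SRS prior to resection, the participant is excluded from the study".
- **Data after discontinuation.** Same section: "In case that the participant discontinues the study, documented medical parameters will not be collected and used for statistical analysis".
- **Replacement.** Statistical analyses: "Patients who dropped out of the study between radiation treatment and first follow-up visit will be replaced by a new patient".
- **Window.** Statistical analyses describes the primary endpoint as "safety assessed from the start of radiotherapy until the first follow up after surgery (4–6 weeks after surgery"). Endpoints has DLTs evaluated "continuously during the study until the first follow-up visit (4–6 weeks after surgery) for each patient and each dose level".
- **DLT list.** In Endpoints and Statistical analyses, hemorrhage appears only as "postoperative hemorrhage (≥ grade 4"). Edema, seizure and headache also need grade 4. Not reaching surgery is not listed.
- **Escalation.** No DLT in three patients leads to the next level, any DLT in the first three leads to three more at the same level, and escalation ends once at least two patients at a level have had a DLT.

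**The concern.** In a neoadjuvant trial, one way for a dose to prove too toxic is that the patient cannot be operated on as planned. The Discussion gives the aim as a dose that allows safe surgery, so this outcome bears directly on the primary question.

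Read together, the rules let such a patient drop out of the dose decision. A resection that is cancelled, or delayed past day 7, departs from the intervention, and departures lead to exclusion. If the patient is instead recorded as having discontinued or dropped out, the data are not used and a new patient fills the place. The end of the safety window cannot rescue the case, because it is counted from an operation that did not take place.

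The patients lost this way are not a random subset. They leave because of something that happened after SRS. Removing them takes events out of the numerator and patients out of the denominator, so the visible DLT rate falls below the true one and the MTD tends to be set too high. With three patients per decision this needs no assumed rate to matter: one uncounted event turns 1/3 (expand) into 0/3 (escalate).

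**Working it through.** **The plan's own figures.** Minimum sample size 4 × [(3 × 3) + 3] = 48 and maximum 4 × 6 × 3 = 72. Both reproduce. They count evaluable patients; replacements would come on top of 72.

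**Inputs.** The escalation rule comes from Statistical analyses. I read it as: pass a level with 0/3, or with 1/3 followed by 0/3. The document gives no toxicity rates, so the following are assumptions:
- a = per-patient rate of ordinary, counted DLTs;
- b = per-patient rate of post-SRS events that stop the planned resection and are not otherwise counted.

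**Formulas.**
- Rate if blocking events count: p = a + b.
- Visible rate if those patients are excluded and replaced: p = a / (1 − b).
- Chance of passing a level below the top: P(p) = (1 − p)³ + 3p(1 − p)² × (1 − p)³.

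**Low case, a = 10%, b = 2%.**
- Counted: p = 0.12, P = 0.681 + 0.190 = 0.871.
- Excluded: p = 0.10/0.98 = 0.102, P = 0.724 + 0.179 = 0.903.
- Shift: about 3 points.

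**Higher case, a = 15%, b = 15%.**
- Counted: p = 0.30, P = 0.343 + 0.151 = 0.494.
- Excluded: p = 0.15/0.85 = 0.176, P = 0.559 + 0.201 = 0.759.
- Shift: about 26 points.

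**Further cases.**

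| a | b | P, counted | P, excluded and replaced | Shift |
|---|---|---|---|---|
| 5% | 5% | 0.906 | 0.971 | 6 points |
| 10% | 5% | 0.814 | 0.897 | 8 points |
| 10% | 10% | 0.709 | 0.887 | 18 points |
| 10% | 20% | 0.494 | 0.862 | 37 points |

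In the last row, if half of the blocking events are listed DLTs and stay in the count, the visible rate is 0.20/0.90 = 0.222 and P = 0.660, a shift of 17 points instead of 37.

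The direction is the same in every case. The size depends on b and on how many blocking events are still counted.

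**Window.** With SRS on day 1 and resection by day 7, the longest regular window ends at 7 + 42 = day 49 (six weeks after surgery). For a patient who is never operated on, the document gives no corresponding day.

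**The case against.** **Exclusion of an unresected patient is an inference.** The only example in the exclusion rule is the reverse case, a patient resected without SRS, and leaving that patient out of an SRS dose-finding count is sensible. No section names a cancelled or delayed resection as a deviation, and Study design ties resection to imaging findings. This stands as a limit on the wording: the text permits the exclusion rather than announcing it. But the example is introduced as an example, the rule is general, and nothing protects patients who have been irradiated.

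**A reader might infer that an unresected patient has no DLT window at all.** The documents do not support that. Safety is assessed from the start of radiotherapy and adverse events continuously, so a listed DLT between SRS and surgery falls inside the window when it occurs. Only the end is undefined.

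**A reader might extend the point to a resection brought forward.** That fails: such a patient has a surgery date and hence a complete window, and an operation on days 2–7 is on schedule.

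**A reader might see a contradiction in Patient selection**, where "The study treatment (neoadjuvant SRS and/or neurosurgical intervention) should be initiated no later than 3 weeks after diagnosis of intracerebral metastases". That sentence sets a deadline for starting treatment. It does not define SRS alone as the complete study treatment.

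**The rates are assumed and the larger ones are high.** This stands. At 2% blocking events the effect is about 3 points. Nor do the documents support a claim that the event stopping surgery would usually fall outside the DLT list.

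**The article condenses a fuller protocol, and a monitoring board reviews adverse events.** Silence on detail would be no finding. Here, however, the exclusion, non-use and replacement rules are printed, each without qualification. Board review at least twice a year is a partial safeguard but does not alter the count that drives escalation.

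**Conclusion.** The point holds in this form: the stated rules allow an irradiated patient who misses the planned resection because of a post-SRS event to be removed from the DLT count and replaced. The text does not say whether a DLT already observed outranks exclusion, and the window has no end for an unoperated patient. The resulting bias is towards escalation.

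Its size is not known from the documents. It is about 3 points in the chance of passing a level at 10% ordinary DLTs and 2% blocking events, and about 26 points at 15% and 15%. A heavier mix gives more; partial counting of the blocking events gives less. These figures assume that all uncounted blocking events lead to exclusion and replacement.

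It would go too far to say that a dose which prevents surgery will be escalated as free of DLTs. That requires either that the event is not a listed DLT or that exclusion overrides a listed one, and the documents settle neither. Because the rules determine the primary endpoint, the wording should be settled before escalation decisions rely on it.

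**What to change.** 1. In Data collection, management, and analysis, limit exclusion from the DLT analysis to participants who received no study SRS.
2. Define the DLT-evaluable set as all participants who received study SRS, and state that a DLT observed before exclusion, discontinuation or dropout always counts.
3. In Statistical analyses, limit replacement to losses unrelated to toxicity.
4. Give the DLT window a fixed end for participants not operated on, for example one matching the longest regular window (about day 49).
5. Ask the investigators to reconcile the DLT list, which names hemorrhage only as postoperative, with a window that opens at radiotherapy and with the aim of safe surgery, and to state how an SRS-related failure to reach resection is classified. That classification is a clinical decision and is theirs to make.

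The cost is protocol wording. The 48 to 72 evaluable patients stay as planned. The small downside is that some dose levels may expand or stop earlier.
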